## Abstract

Percutaneous electrolysis consists of the application of a galvanic electrical current throughout an acupuncture needle. It has been previously hypothesized that needling procedures’ neurophysiological effects may be related to endogenous pain modulation (EPM). This protocol study describes the design of a double-blind (participant, assessor) randomized controlled trial with the aim to investigate whether percutaneous electrolysis is able to enhance EPM and whether the effect is different between two applications depending on the dosage of the galvanic electrical current. Seventy-two asymptomatic subjects not reporting the presence of pain symptoms the previous 6 months before the study, aged 18–40 years, are randomized into one of four groups: a control group who does not receive any intervention, a needling group who receives a needling intervention without electrical current, a low-intensity percutaneous electrolysis group (0.3 mA × 90 s), and a high-intensity percutaneous electrolysis group (three bouts of 3 mA × 3 s). Needling intervention consists of ultrasound-guided insertion of the needle on the common extensor tendon of the lateral epicondyle. The primary outcome is conditioned pain modulation (CPM), and secondary outcomes include widespread pressure pain sensitivity (pressure pain thresholds (PPT) over the lateral epicondyle, the cervical spine, and the tibialis anterior muscle) and temporal summation (TS). We expected that percutaneous electrolysis would have a greater influence on CPM than an isolated needling procedure and no intervention. In addition, we also postulated that there might be differences in outcome measures depending on the intensity of the electrical current during the percutaneous electrolysis application. This study makes a new contribution to the field of neurophysiological effects of percutaneous electrolysis and needling interventions.

## 1. Introduction

Percutaneous electrolysis is a minimally invasive approach consisting of the application of a galvanic current throughout an acupuncture needle [1,2,3]. The needle is placed directly into soft tissue structures, usually ultra-sound guided. This technique involves the combination of the mechanical stimulation produced by the needle and the electrical/biochemical stimulation provided by the electrical current [4,5,6]. 

Scientific evidence concerning percutaneous electrolysis has increased in the last decade. In fact, a recent meta-analysis has found moderate-quality evidence suggesting a positive effect of percutaneous electrolysis for improving pain and related disability in musculoskeletal pain conditions [7]. One weakness of this meta-analysis was the inclusion of heterogeneous chronic pain conditions, such as patellar tendinopathy, shoulder pain, whiplash syndrome, or temporo-mandibular pain [8,9,10,11,12,13]. 

The exact underlying mechanisms behind the effects of percutaneous electrolysis are not fully understood. It has been proposed that a galvanic current in a saline solution generates a chemical process (“electrolysis”), causing the dissociation of the molecules of sodium chloride and water and producing non-thermal electrochemical ablation [8,14,15]. This organic reaction might be able to stimulate a localized and controlled inflammatory response, hence promoting proper healing of the tissue [5,15,16]. However, this hypothesis is not scientifically supported to date, and although several mechanisms and effects are attributed to percutaneous electrolysis, currently there are few publications on this topic. The application of percutaneous electrolysis in collagenase-induced tendinopathy in rats has been able to produce an increase in expression of anti-inflammatory and angiogenic molecules [16] and an increase in the expression of some genes associated with collagen-remodeling of extracellular matrix [17]. Similar results were found in notexin-induced muscular injury in rats; the application of percutaneous electrolysis produced a decrease in pro-inflammatory mediators and an increase in the expression of anti-inflammatory proteins and vascular endothelial growth factor [15]. In humans, percutaneous electrolysis causes a parasympathetic activity (detected by hearth-rate variability) due to the combination of needle puncture and electric current [1,2]. 

Thus, the exact therapeutic mechanisms of percutaneous electrolysis are not completely defined, and both mechanical and biochemical effects are currently suggested [9]. Recently, it has been hypothesized that dry needling may produce neurophysiological effects integrated into a pain neuroscience paradigm, such as activation of central inhibitory pain pathways, analgesia, conditioned pain modulation, segmental inhibition, or release of endogenous opioids and other neurotransmitters [18,19,20]. These mechanisms should be included in the concept of endogenous pain modulation (EPM), which is the ability of the central nervous system to modulate the nociceptive input from peripheral tissues ascending from the spinal cord to the brainstem [21].

Endogenous pain modulation shows a clinical relevance and plays an important role in the experience of pain. In fact, although the intensity of a nociceptive input is significant for pain, the subsequent modulation of peripheral impulses conditions the intensity of the final painful sensation [22]. In this way, dysfunction of pain inhibitory ability has been associated with chronic pain states such as fibromyalgia, osteoarthritis, or temporomandibular disorders [23]. Further, it has been proposed that EPM efficacy may predict the analgesic effect in response to treatment and that even some therapies are able to potentiate the EPM [24]. No study has investigated the effects of percutaneous electrolysis in EPM. 

The primary aim of this randomized clinical trial is to investigate if the application of percutaneous electrolysis enhances EPM when compared with a simple needle application or no intervention in an asymptomatic healthy population. The secondary aim is to determine if the effects on EPM are different between the application of two different protocols (i.e., low intensity or high intensity of the electrical current) of percutaneous electrolysis. Thus, we first hypothesize that a single session of percutaneous electrolysis will be able to activate EPM in a greater manner than the application of dry needling. Our second hypothesis is that activation of EPM will be higher with the high-intensity protocol than with the low-intensity protocol.

## 2. Materials and Methods

### 2.1. Study Design and Setting

A double-blind randomized controlled trial at the Faculty of Nursing and Physiotherapy, University of Salamanca (Spain) was conducted according to the Consolidated Standards of Reporting Trials (CONSORT) Statement [25]. The current treatment protocol is described according to the recommendations of SPIRIT [26]. 

The protocol of this trial received approval from the Ethics Committee of University of Salamanca (record number 2021/550), and was be conducted according to the Declaration of Helsinki. The clinical trial was registered in ClinicalTrials.gov (registration number NCT04710992).

### 2.2. Participants and Eligibility Criteria 

Participants were recruited from the general population by local advertisements. The participants of this study were asymptomatic adults, aged 18 to 49 years, of both genders, not reporting the presence of pain symptoms the previous 6 months before the study. Volunteers were contacted by email, and those who meet the eligibility criteria were included. All subjects signed a written informed consent before collecting any data.

Participants were excluded if the following were present: 1, belonephobia (fear of needle), 2, neurological, cardiovascular, or metabolic diseases; 3, any medical conditions causing pain; 4, cutaneous alterations; 5, pregnancy; 6, cognitive or sensitivity disorders; 7, fibromyalgia syndrome; 8, frequent/regular consumption of alcohol and other drugs; 9, had received any medication or physical therapy treatment the previous week; 10, intake of caffeine in the two hours prior to measurement; or, 11, vigorous physical activity on the day of testing.

### 2.3. Interventions

This randomized clinical trial had four groups: control group who did not receive any intervention, needling group who received a needling intervention, low-intensity percutaneous electrolysis group who received the intervention for a longer period of time with low intensity of the electrical current (0.3 mA × 90 s), and high-intensity percutaneous electrolysis group who received the intervention for a shorter period of time with high-intensity electrical current (3 bouts of 3 mA × 3 s). All interventions were performed by a physical therapist with more than 10 years of experience in the technique. 

The control group did not receive any intervention for 5 min (time period similar to the remaining groups). The remaining groups received a single session of an ultrasound-guided needle intervention on the common extensor tendon of the lateral epicondyle of their dominant side. Participants were comfortable in a supine position with the dominant elbow on the table in a position of 20° flexion and with the forearm pronated. As described by Rodríguez-Huguet et al. [27], a 25 × 0.3 mm acupuncture needle (Agupunt, Barcelona, Spain) was inserted ultrasound-guided 45° to the skin towards the lateral epicondyle to reach the deep surface of the common extensor tendon. The technique of inserting the needle and the time it is embedded into the participant’s tissues were the same for all groups (90 s) for avoiding different mechanical effect of the needle. The three procedures only differed in the application or not of the electrical current and the intensity of the galvanic current that was applied through the needle. 

The needling group received just the needing intervention without the application of any electrical current. The needle was ultrasound-guided inserted into the common tendon of the lateral epicondyle and left in situ for 90 s without galvanic current. This needling procedure has been previously used in a randomized clinical trial investigating the effects of percutaneous electrolysis in people with plantar heel pain [28].

The low-intensity percutaneous electrolysis group received the intervention for a longer period of time with low intensity of the electrical current. Percutaneous electrolysis was applied using a certified medical device (EPI^®^-Alpha, Barcelona, Spain). Once the needle was ultrasound-guided inserted into the common tendon of the lateral epicondyle, a galvanic current with an intensity of 0.3 mA for 90 s will be applied (total electrical charge applied according to the Coulomb Law: 27 mC). These parameters of electrical current had been previously applied in two previous randomized clinical trials investigating the effect of percutaneous electrolysis in people with shoulder pain [9,10]. 

The high-intensity percutaneous electrolysis group received the intervention for a shorter period of time with high intensity of the electrical current. Percutaneous electrolysis was applied with the same certified medical device as in the low-intensity group (EPI^®^-Alpha, Barcelona, Spain). First, the needle was ultrasound-guided inserted into the common tendon of the lateral epicondyle. During the first 75 s of the application, no electrical current was applied. At the end of the session, three applications of 3 s each at an intensity of 3 mA (total electrical charge applied according to the Coulomb Law: 27 mC) of the galvanic electrical current were applied. These parameters had been previous used in clinical trials investigating the effects of percutaneous electrolysis [12,29]. The round electrode was placed in the lower third of the humerus as closest as possible to the elbow.

### 2.4. Outcomes

All outcomes were evaluated before (2 min) and immediately after (2 min) the intervention by an assessor blinded to the treatment allocation group. The experiment always took place in the same quiet room with a similar temperature and schedule for all participants. Before the baseline outcomes, the following socio-demographic variables were assessed: age (years), gender (male or female), weight (kg), height (m), body mass index (BMI) (kg/m^2^), smoking (yes or no), and level of physical activity (measured by the short version of the International Physical Activity Questionnaire (IPAQ-SF)) [30]. The order of outcome assessment was always the same: widespread PPTs, CPM and TS.

#### 2.4.1. Primary Outcome

The primary outcome was conditioned pain modulation (CPM), which was tested using the upper extremity submaximal effort tourniquet test [31]. Specifically, participants were asked to elevate their non-dominant upper extremity for one minute. A blood-pressure cuff was inflated to a pressure of 280 mm Hg. Participants rated the tourniquet-induced pain intensity of the upper extremity on an 11-point numerical pain rate scale (NPRS, 0–10). The cuff was deflated 6 min after, and 3 trials of pressure pain thresholds (PPTs) at the extensor tendon of the lateral epicondyle, cervical spine, and tibialis anterior muscle were obtained immediately following cuff deflation. Activation of CPM was operationally defined as an increase in PPTs of at least 10% following the conditioning stimulus (tourniquet test). These methods correspond to recommendations on practice of CPM testing [31].

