#### 2.4.2. Secondary Outcome

The secondary outcomes included widespread pressure pain sensitivity and temporal summation. All outcomes were assessed by using a digital pressure algometer (Force One FDIX, Wagner Instruments, Greenwich, CT, USA) with a round rubber surface of 1 cm^2^. Participants were supine. Algometry measurements were conducted at the following three locations bilaterally in the following order: common extensor tendon at the lateral epicondyle, tibialis anterior, and cervical spine. These locations were marked with a pen to assess all measurements at the same points.

Widespread pressure pain sensitivity was assessed by determining PPTs bilaterally in the treatment point (elbow), segmental-related point (cervical spine), and a distant non-related point (tibialis anterior). The pressure was applied perpendicular over each point at a rate of 1 kg/s approximately until the subject felt the first sensation of pain [32,33]. At this moment, the algometer was removed and the measurement value was recorded. Participants had two practice trials on the hand before the evaluation begins. Three measurements were obtained at each assessed point with a 30-s interval for avoiding temporal summation [34] and the mean was used for the analysis. If there was a difference of more than 1 kg/cm^2^ between two consecutive measurements at the same point, the highest value was removed and another measurement was obtained.

The evaluation of temporal summation (TS) began one minute after the end of the CPM assessment. The sequential stimulation of mechanical pressure stimuli consisted of 10 pressures with the algometer at PPT level (with 1-s interval between them) on each of the three assessed points, i.e., elbow, neck, and tibialis anterior [35]. The subjects were asked for rating their pain of the 1st and 10th pulse on a numerical pain rating scale (NPRS; 0 = no pain, 10 = maximum tolerable pain). The final rating of TS resulted from the difference between the 10th and the 1st pain rating scores [36]. Figure 1 graphs the experimental protocol timeline.

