### 2.5. Sample Size 

The sample size was calculated for the primary outcome. Overall, an increase of at least 10% in PPTs following the conditioning stimulus was considered as an activation of CPM [31]. The determinations were based on detecting pre-post differences of 20% on PPTs following the conditioning stimulus with an alpha level of 0.05, and a desired power of 80%. This generated a sample size of at least 16 participants per group. Similarly, we calculated sample size according to clinically relevant changes. We estimated a large effect size of 1.05 (Cohen’s d) for changes in PPTs following the conditioning stimulus with a statistical power of 80% and an alpha error of 0.05. Therefore, we estimated 16 subjects per group, and considering a 10% lost, 18 individuals per group were recruited (72 subjects in total). GPower 3.1 program was used to calculate the sample size [37].

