### 2.8. Statistical Methods 

Data were analyzed by using the IBM-SPSS software package (version 26.0). The significance threshold was established at 0.05 and the limits of the confidence interval at 95%. Changes in outcomes were tested on the basis of the intention-to-treat principle. Firstly, the distribution of normality for all the variables was checked by the Shapiro–Wilk test. Then, a descriptive analysis of baseline characteristics of the sample was reported, calculating the means and standard deviations for those variables with normal distribution and the median and interquartile range for those with non-normal distribution.

Subsequently, to assess the effects of the interventions, we conducted repeated measures analysis of variance (ANOVA) tests for quantitative variables (or Kruskal–Wallis test for non-normal variables) and the Bonferroni test as post hoc comparisons. Mixed-effect regression models considering the group effect, time effect, and group x time interaction were conducted. 

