### 3.2. Limitations

It should be recognized that this protocol has some limitations. First, this study will include healthy participants, which will make it difficult to extrapolate the results to daily clinical practice. Nevertheless, we consider that it is highly important to determine the physiological effects of an intervention such as percutaneous electrolysis first in healthy individuals showing proper CPM and as a second step to determine its effects in different chronic pain conditions, where CPM is usually impaired and, therefore, the response maybe different. Second, another consideration is the inclusion of a non-intervention group to determine the effects of time on CPM. Additionally, although the participants will be blinded from their group assignment, some subjects may perceive discomfort related to the application of galvanic current and identify the intervention that they receive. Successfully blinding will be confirmed by asking the participants which intervention they believed had received. It should be recognized that it will be not possible to blind the therapist who will apply the interventions, considering the treatment approach that is proposed. It would increase the risk of bias due to deviation from intended interventions. Finally, the results of this study will be restricted to the immediate effects of assessments. Since this is a mechanisms-related study, this is the common procedure in published studies [40,41,42].

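### The single primary outcome, CPM, is measured at three non-equivalent PPT sites with no lead site, combining rule or settled scale, so the primary result is not fixed in advance

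*Protocol article*

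**What the plan says.** Section 2.4.1 gives one primary outcome, CPM, assessed with a tourniquet on the non-dominant arm. After deflation, "3 trials of pressure pain thresholds (PPTs) at the extensor tendon of the lateral epicondyle, cervical spine, and tibialis anterior muscle were obtained". The section then adds a threshold: "Activation of CPM was operationally defined as an increase in PPTs of at least 10% following the conditioning stimulus". It does not say at which site or sites the threshold must be met, or on which side of the body the readings are taken.

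Section 2.4.2 gives each site its own role: the elbow is where treatment is applied, the cervical spine is segmentally related, and the tibialis anterior is remote and unrelated. It averages repeat readings within a point but gives no rule across points. It also states "Algometry measurements were conducted at the following three locations bilaterally in the following order", under the secondary outcomes.

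Section 2.5 repeats the 10% definition but sizes the trial on "detecting pre-post differences of 20% on PPTs following the conditioning stimulus", "with an alpha level of 0.05, and a desired power of 80" per cent. It then gives a second basis: "We estimated a large effect size of 1.05" (Cohen's d). Neither basis names a site.

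In section 2.8, "The significance threshold was established at 0.05". Quantitative variables go to repeated measures ANOVA (Kruskal–Wallis if non-normal), Bonferroni is the post hoc procedure, and mixed models with a group-by-time term are also planned.

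**The concern.** A primary outcome should point to one number, or to a stated rule that turns several numbers into one decision. Here the plan yields three CPM results, one per site, and does not say which of them answers the primary question.

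The choice matters because the sites are not replicates. A change at the tibialis anterior, far from both needle and cuff, supports a different claim from a change at the tendon that has just been needled. A positive result at one site and null results at the other two could be reported as a positive primary outcome, and nothing in the article would contradict that.

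The scale is also open. The 10% activation rule and the continuous change used for sizing are different variables and need not agree. Meanwhile the sample size spends the whole 0.05 on a single comparison, which leaves no allowance for several chances of success.

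**Working it through.** **1. Reproduce the plan's sample size.** Inputs from section 2.5: d = 1.05, alpha 0.05, power 80%, 10% loss.

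- Two-sample t-test, two-sided 0.05, noncentral t: n = 15.26, so 16 per group. Power is 0.820 at 16 and 0.793 at 15.
- Variants that do not match: one-sided gives 12 per group; a paired test gives 10.
- Loss: 16 / (1 − 0.10) = 17.8, so 18 per group; 4 × 18 = 72.

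The stated figures are reproduced. They correspond to one two-group comparison of one continuous variable at the full 0.05. The 20% basis cannot be checked because no standard deviation is given.

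**2. Chance of at least one false-positive omnibus result if any site may count.** With two time points, the group-by-time test at one site is the same as a one-way F test on the change scores. With 4 groups of 16 this has 3 and 60 degrees of freedom.

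- Independent sites, by formula: 1 − (1 − 0.05)^3 = 1 − 0.857 = 14.3%.
- Correlated sites, by simulation under no group effect (20,000 runs; the common between-site correlation is assumed, since the article gives none):

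| Assumed correlation | At least one of three sites significant |
|---|---|
| 0 | 14.1% |
| 0.3 | 13.9% |
| 0.5 | 12.7% |
| 0.7 | 11.1% |
| 0.9 | 8.3% |

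A single site gave about 5% throughout, as it should. Bonferroni on post hoc group contrasts does not change these figures, because it acts within one site's analysis.

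**3. If CPM were also measured on both sides (not stated in section 2.4.1).** Six readings: 1 − 0.95^6 = 26.5% if independent, and about 11% at correlation 0.9.

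**4. Cost of keeping three co-primary sites.** The first Holm step uses 0.05/3 = 0.0167, the same level as Bonferroni. With d = 1.05:

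- Power at 16 per group: 66.8%, against 82.0% at 0.05. At 18 per group: 73.3%.
- For 80% power at that level: n = 20.5, so 21 per group; 21 / 0.90 = 23.3, so 24 per group; 4 × 24 = 96.

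**5. One named site and scale.** The error rate is 5%, and the requirement stays at 16 per group, 18 with loss, 72 in total.

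**The case against.** The strongest reply is that the article states no any-site success rule. An average over sites, or a requirement that all sites be positive, would not inflate the error, and a SAP that is not shown may contain such a rule. This stands: the inflation is conditional, and a reader who infers that the type I error simply exceeds 5% goes further than the text. It does not remove the point. Defining the primary outcome is the protocol's task, and the article does define it, at three sites of different kinds and with a threshold that its sample size does not use.

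Four other inferences are tempting and not supported:

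- **Six primary readings, one elbow on the cuffed arm.** This rests on the bilateral wording in section 2.4.2. Section 2.4.1 does not say that the CPM readings are bilateral.
- **A yes/no outcome analysed by ANOVA.** Section 2.8 assigns ANOVA to quantitative variables and names no test for activation. The yes/no form is an open option, not a planned test.
- **An elbow result is invalid.** CPM is assessed before and after the intervention, with unconditioned PPTs taken each time. A local shift enters both the conditioned and the unconditioned reading and may partly cancel. The introduction also counts segmental inhibition as endogenous modulation. Ambiguous is the right word.
- **Most volunteers already pass the 10% rule.** The article does expect "healthy individuals showing proper CPM". However, any percentage requires treating the 20% and d = 1.05 as the mean and standardised size of the same baseline quantity. Section 2.5 presents them as separate calculations, and the 16 per group comes from a two-sample test, so d behaves as a between-group effect. No baseline mean or SD is given.

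**Conclusion.** The point holds in a limited form: the article does not fix a single primary variable. Site, side and scale are open, the three sites are not interchangeable, and 0.05 is not divided among them. If any site may count, the chance of at least one false-positive primary omnibus test is about 8% to 14%, for assumed between-site correlations from 0.9 down to 0. It would be higher if CPM were also bilateral.

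The sample size is not wrong on its own inputs; it is adequate for one continuous variable at one site. The defect should be corrected and is cheap to correct. It does not show that the trial's error rate is in fact above 5%.

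**What to change.** Before unblinding, and with a date, name one continuous CPM variable as primary: the change, from before to after the intervention, in conditioned relative to unconditioned PPT, at one stated site and side. The dominant-side tibialis anterior is a reasonable choice because it is remote from both the needle and the cuff; another site can be justified if the reason is given. Make the other sites secondary and use the 10% activation rule descriptively only. If elbow CPM is reported, describe a change there as ambiguous between local and endogenous effects.

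The cost is wording in sections 2.4.1 and 2.8. The total of 72 is unchanged, and the small downside is that the other sites lose primary status.

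If all three sites are to stay co-primary, apply Holm across them and restate the power: about 67% instead of 82% at 16 per group for the first step, or 96 participants to restore 80% at that step.

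### The single primary outcome, CPM, is read at three body sites with no primary site or combining rule, while the significance level and sample size are set as if for one reading

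*Protocol article*

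**What the plan says.** - **Outcome.** Section 2.4.1 makes CPM the primary outcome. After the tourniquet, "3 trials of pressure pain thresholds (PPTs) at the extensor tendon of the lateral epicondyle, cervical spine, and tibialis anterior muscle were obtained". Success is described by one sentence: "Activation of CPM was operationally defined as an increase in PPTs of at least 10% following the conditioning stimulus". It does not say at which site, or whether one site or all sites must show the rise.
- **Averaging.** Section 2.4.2 says "Three measurements were obtained at each assessed point with a 30-s interval", and the mean is analysed. That averages repeats within a point, not across sites. The same section gives the sites different roles: treated, segmentally related, and distant and unrelated.
- **Sides.** Section 2.4.2 also says "Algometry measurements were conducted at the following three locations bilaterally". Section 2.4.1 does not say whether this applies to the CPM readings.
- **Analysis.** Section 2.8 states: "The significance threshold was established at 0.05 and the limits of the confidence interval at 95" per cent. It names repeated-measures ANOVA, with "the Bonferroni test as post hoc comparisons", and mixed models with group, time and their interaction. There is no site term.
- **Sample size.** Section 2.5 opens: "The sample size was calculated for the primary outcome". It uses an effect size of 1.05, alpha 0.05 and 80% power, giving 16 per group, or 18 after 10% loss (72 in total).

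**The concern.** The outcome definition produces three CPM results per participant, but the error rate and the sample size are set for one. No composite is defined and the model has no site term, so the most natural way to run it is once per site. The only stated correction follows the ANOVA and is most naturally read as covering pairs of arms. Nothing extends it to sites.

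Two things are at stake. First, a chance finding at one of three sites could be presented as the primary result. Second, if the sites disagree, for example an effect at the elbow but none at the tibialis anterior, the article does not say what the answer to the primary question is.

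**Working it through.** **1. The plan's own figure.** Inputs from section 2.5: d = 1.05, alpha 0.05, power 80%. A two-sided two-sample t-test needs n = 15.26, so 16 per group (power 82.0% at 16). Allowing for 10% loss, 16 / 0.9 = 17.8, so 18; 4 × 18 = 72. The figure reproduces as a single two-sided comparison. A one-sided test would need 12 per group and a paired test 10, so neither explains 16.

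**2. Three sites, any one sufficing, if independent.** 1 − (1 − 0.05)³ = 1 − 0.857 = 14.3%.

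**3. Correlated sites.** The article gives no inter-site correlation, so a range is assumed. The simulation used no true effect, four arms of 18, and equally correlated normal changes at each site. With one pre and one post value, the group F-test on the change is the group-by-time test. Adjusted pairs were tested at 0.05/6. The table gives the chance of at least one significant site.

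| Inter-site correlation | Omnibus F at 0.05 | Any Bonferroni-adjusted pair | Adjusted pair favouring electrolysis over needling or control |
|---|---|---|---|
| 0 | 14% | 12% | 4.4% |
| 0.5 | 13% | 11% | 3.8% |
| 0.7 | 11% | 9–10% | 3.5% |
| 0.9 | 9% | 7% | 2.6% |
| One site only | 5% | 4% | about 1.5% |

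The last column is closest to the aim in section 1. Against 1.5%, the ratio runs from 2.6 / 1.5 = 1.7 to 4.4 / 1.5 = 2.9, roughly two to three times.

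**4. If CPM were also read on both sides.** Six readings give 1 − 0.95⁶ = 26.5% if independent. By simulation, the omnibus rate is about 22% at correlation 0.5, 17% at 0.7 and 11% at 0.9.

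**5. Other decision rules.** If all three sites had to succeed, or one averaged score were tested, the rate would be at most 5%.

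**6. Cost of correcting across sites instead.** With Bonferroni over three sites, alpha is 0.05/3 = 0.0167. Power at 16 per group falls from 82% to about 67%, and at 18 per group it is 73%. Restoring 80% needs 21 per group, or 24 with loss (21 / 0.9 = 23.3), which is 96 in total.

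**The case against.** The strongest objection is that the any-site rule is not in the text. Section 2.8 gives a general threshold and does not say that the sites are analysed separately. Section 2.4.1 speaks of PPTs collectively, and a condensed article may leave the handling of several sites to a fuller document. This stands against any unconditional error rate. It does not dispose of the point, because the article does define its primary outcome, and that definition gives three readings where section 2.5 plans for one.

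A reader might infer that the chance of a false primary claim is 11–14% rather than 5%. The documents do not support that. The range is for the omnibus test under an assumed correlation of at most 0.7, and a significant omnibus test does not by itself show that electrolysis is better. It also counts needling against control, one intensity against the other, and results against electrolysis. For an adjusted result favouring electrolysis, the rate stays below 5% at three sites even under the any-site rule.

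A reader might also infer six primary readings. The bilateral statement is in the secondary-outcome section, and section 2.4.1 does not apply it to CPM.

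The between-arm Bonferroni step does not remove the problem: 7–12% for any adjusted pair is still well above the 4% for one site.

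**Conclusion.** The concern holds in conditional form. The primary outcome is not reduced to one reading, and the sample size and threshold assume that it is. If each of three sites is tested at 0.05 and any one suffices, the chance of at least one significant group effect under no true effect is about 9–14% (omnibus) or 7–12% (any adjusted pair), for inter-site correlation from 0.9 down to 0. It would be higher if the CPM readings are bilateral. A false adjusted result favouring electrolysis is about 3–4%.

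These figures rest on the assumed correlation, the inferred any-site rule, normal data and 18 per arm. The sample size is correct on its own inputs. The defect is that those inputs are not attached to a particular reading.

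**What to change.** Before unblinded analysis, state in sections 2.4.1 and 2.8 which CPM quantity is primary. Either of these would do:

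- one reading, with its side stated, for example the tibialis anterior, which section 2.4.2 describes as the distant unrelated point; or
- one pre-specified mean across the three sites.

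Make the individual remaining sites secondary, say whether CPM is read on one side or both, and state in section 2.5 that the effect size of 1.05 refers to the chosen quantity. This restores 5% for the primary group test and, with 1.05 kept for that quantity, leaves 18 per group unchanged.

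The cost is a few sentences and no new data. The downside is that an effect seen at only one non-primary site no longer counts as primary success. Correcting across the three sites instead is possible but not free: the loss of power in step 6 would have to be stated and accepted, or the sample enlarged.
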